### Sample Size

The primary endpoint will be the CAR from weeks 9-24. We estimated conservatively 52.8% in the CASC treatment group and 40.8% in the control group as the primary endpoint (CARs from weeks 9-24) based on the survey of smoking cessation [22]. Regarding the effect size, we referred data from a clinical trial of maintenance therapy with varenicline [7], which indicated that 24 weeks of varenicline therapy showed 12% of additional abstinence rate than placebo in the total population. Thus, we estimated that 24 weeks of the CASC intervention could obtain additional effect of 12% on abstinence rate compared with the control group. A sample size of 290 in each treatment group will have 80% power using a chi-square test with a 2-sided significance level of .05 (nQuery Advanced 8.2.1).

### Statistical Analysis

All statistical analyses will be performed according to the intention-to-treat principle and using 2-sided at a .05 significance level. The baseline characteristics will be described by the mean and SD, median and quantiles (continuous variables), or proportion (categorical variables). We will examine the outcomes using the full analysis set. For the primary outcome, we will compare CARs from weeks 9-24 comparing the CASC treatment group and the control group using a logistic regression model adjusted for prescribed smoking cessation medications. In addition, secondary outcomes at each defined period will be evaluated with logistic regression analysis adjusted for appropriate covariates between the groups. We will provide descriptive statistics, odds ratios, 95% CIs, and *P* values for each outcome. A statistical analysis plan detailing all statistical computations will be completed prior to the lock of the database. SAS statistical software, version 9.4 or upper version (SAS Institute Inc), will be used for all the analyses.

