### Randomization

Randomization will be performed for eligible participants. They will be allocated 1:1 to both arms—the CASC treatment group and the control app group. Randomization will be performed by a computer-generated random sequence with stratification for smoking cessation medications.

**Table 1 table1:** The list of trial centers.

Number	Institution	Prefecture
1	Ankou Medical Clinic	Tokyo
2	Ayano Clinic	Saitama
3	BOOCS Clinic Fukuoka	Fukuoka
4	Chuo Naika Clinic	Tokyo
5	Ebisu Garden Place Clinic	Tokyo
6	Higashi-hie Naika	Fukuoka
7	Hosoda Shinryojo (clinic)	Tokyo
8	Inoue Naika Clinic	Ibaraki
9	Kanda Clinic	Tokyo
10	Keio University Hospital	Tokyo
11	Kimura-Shiro Clinic	Fukuoka
12	Kita Shin-Yokohama Naika Clinic	Kanagawa
13	Mashiba Iin (clinic)	Saitama
14	Maekawa Medical Clinic	Kanagawa
15	Miyazaki RC Clinic	Tokyo
16	Motosumiyoshi Kokoromi Clinic	Kanagawa
17	Nakameguro Atlas Clinic	Tokyo
18	National Center for Global Health and Medicine	Tokyo
19	Nemoto Geka-Seikeigeka (clinic)	Saitama
20	Nihonbashi Naika-Allegy Clinic	Tokyo
21	Nomura Iin (clinic)	Tokyo
22	Odayaka Life Naika Clinic	Saitama
23	Saitama City Hospital	Saitama
24	Sawayama Naika-Sougoushinryou Clinic	Fukuoka
25	Segawa Hospital	Saitama
26	Shimizu Clinic Fusa	Saitama
27	Shinjuku Research Park Clinic	Tokyo
28	Sone Clinic Shinjuku	Tokyo
29	Tajima Clinic	Tokyo
30	Tenjin Sogo Clinic	Fukuoka
31	Ueda Naika Clinic	Fukuoka

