### Follow-Up Schedule

Table 2 shows the overall follow-up schedule of this trial. At registration, patients’ background profile, exhaled CO concentration, nicotine dependence, and smoking status will be assessed using instruments such as the Tobacco Dependence Screener [21], Brinkman index (multiplied by cigarettes per day and years of smoking), Fagerström Test for Nicotine Dependence (FTND), FTCQ-12, KTSND, and MPSS. The background profile includes age, sex, body weight, years of smoking, cigarettes per day, and medical history at the initiation of device use. Regular follow-up visits will be scheduled at 2 weeks (±7 days), 4 weeks (±7 days), 8 weeks (±14 days), 12 weeks (±14 days), 24 weeks (±28 days), and 52 weeks (±28 days); during these follow-up visits, we will examine patients’ scores regarding FTCQ-12, KTSND (after 8 weeks), and MPSS, as well as exhaled CO concentration, status of nonsmoking, status of device use, and adverse events. Adverse events and concomitant pharmacological therapy will be recorded through the trial.

An independent monitoring staff will conduct on-site data monitoring. In addition, the staff will review trial database to confirm whether principal and subinvestigators at each clinic perform the clinical trial according to the research proposal and standard operation procedures, and data queries will be asked if necessary.

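### The primary model is valid, but it leaves out dependence measures already collected at Day 1, and no risk difference with a confidence interval is named beside the odds ratio

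*Protocol article*

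**What the plan says.** All of this is in the protocol article.

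- **Primary model (Statistical Analysis).** The two groups' abstinence rates are compared "using a logistic regression model adjusted for prescribed smoking cessation medications". For secondary outcomes the covariates are left open. For the primary outcome, one covariate is fixed.
- **Stratification (Randomization).** "Randomization will be performed by a computer-generated random sequence with stratification for smoking cessation medications". No other factor is named.
- **Baseline data (Table 2 and Follow-Up Schedule).** FTND and exhaled CO are both taken on the day of registration. Cigarettes per day is part of the background profile.
- **Sizing (Sample Size).** "We estimated conservatively 52.8% in the CASC treatment group and 40.8% in the control group as the primary endpoint", which is an "additional effect of 12% on abstinence rate compared with the control group".
- **Reporting (Statistical Analysis).** Each outcome gets descriptive statistics, odds ratios, 95% CIs and P values. The odds ratio is the only between-group effect measure named. A separate SAP is to be finished before database lock.

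**The concern.** Two things can be improved here.

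First, the condition treated is nicotine dependence, and its severity is measured before treatment starts. It is reasonable to expect severity to predict abstinence. If it does, a primary model without it gives up some precision and does not correct a chance imbalance in severity between the arms. Stratification by medication alone does not correct one either.

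Second, the planning quantity is a difference of 12 percentage points, but the effect measure named is an odds ratio. With success rates of 41-53% the two scales look very different, and a reader who takes an odds ratio of 1.62 for a risk ratio would overstate the benefit. Nothing named in the article would show how precisely the 12-point difference has been estimated.

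**Working it through.** **Inputs from the article:** 40.8% (control) and 52.8% (CASC), 290 per arm, two-sided 0.05, 80% power, chi-square test, 1:1 allocation. **Assumed:** the strength of the baseline covariates, because the article gives none.

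**1. The plan's own figure.** With mean rate 0.468, 2 × 0.468 × 0.532 = 0.49795. The sum of the two binomial variances is 0.528 × 0.472 + 0.408 × 0.592 = 0.49075.

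n = (1.960 × √0.49795 + 0.8416 × √0.49075)² / 0.12² = 271 per arm, or 287 with the continuity correction. Power at 290 per arm is 82.7% without the correction and 80.5% with it. The stated 290 therefore reproduces to within 3 participants per arm with the correction, and the stated power is met without further covariates.

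**2. The planned effect on three scales.**
- Risk difference: 0.528 − 0.408 = 12.0 points. Its SE is √(0.49075/290) = 4.1 points, so the 95% CI would be about 12.0 ± 8.1.
- Risk ratio: 0.528/0.408 = 1.29.
- Odds ratio: (0.528/0.472)/(0.408/0.592) = 1.62.

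An odds ratio of 1.62 equals 12.0 points at a control rate of 40.8%. It equals 11.0 points at 30%, 11.9 at 50%, 10.9 at 60% and 10.1 at 65%. The odds ratio alone does not say whether 12 points was reached. Together with the group proportions it does, apart from the interval for the difference.

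**3. Power with a baseline covariate.** 4,000 trials were simulated per row, with 290 per arm and a logistic Wald test. Marginal rates were held at 40.8% and 52.8%. One standardised normal score stands in for the baseline measures, and no medication term was included.

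| Assumed log OR per SD (OR) | AUC | Power without score | Power with score | Gain, points | Adjusted OR | Fall in variance of standardised risk difference |
|---|---|---|---|---|---|---|
| 0 (1.00) | 0.50 | 81.8% | 81.4% | −0.3 | 1.62 | none |
| 0.3 (1.35) | 0.58 | 83.2% | 84.5% | 1.3 | 1.65 | 2% |
| 0.5 (1.65) | 0.64 | 83.4% | 85.1% | 1.7 | 1.68 | 5% |
| 0.7 (2.01) | 0.69 | 81.8% | 85.7% | 3.9 | 1.72 | 11% |
| 1.0 (2.72) | 0.74 | 82.5% | 89.2% | 6.7 | 1.80 | 18% |

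Gains were taken before rounding. The simulation error of each power is about √(0.82 × 0.18/4000) = 0.6 points, which explains why the column without the score varies. The standardised risk difference stays at about 12 points in every row.

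A second simulation (3,000 trials per setting) compared medication only with medication plus one covariate. Power rose from 82.5% to 83.3% at an odds ratio of 1.3 per SD, from 81.0% to 82.8% at 1.5, from 83.2% to 85.2% at 1.7, and from 82.0% to 85.6% at 2.0. The two simulations agree on about 1 to 4 points for 1.3 to 2.0 per SD.

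As a yardstick, a 5% fall in variance is worth 580 × (1/0.95 − 1) = about 30 participants.

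**4. Chance imbalance.** The SE of the between-arm difference in a standardised covariate is √(2/290) = 0.083 SD. A two-SE imbalance is 0.166 SD. At an assumed log OR of 0.5 per SD it shifts the treatment log odds ratio by 0.083, against a planned ln 1.62 = 0.48. On the risk scale this is about 0.083 × 0.468 × 0.532 = 0.02, or 2 of the 12 points.

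**The case against.** The case against is substantial, and most of it stands.

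- **The stated model is sound.** It adjusts for the one named stratification factor and meets the stated power. Randomisation protects the type I error, and the test already allows for chance imbalance. A reader might infer that leaving out FTND makes the analysis biased or underpowered. The article's own figures do not support that (80.5% or 82.7% at 290 per arm).
- **The odds ratio will not stand alone.** A reader might infer that the plan reports nothing else. The same sentence promises descriptive statistics, which for a yes/no outcome would normally give each arm's rate and so the crude difference. What is not named is a confidence interval for that difference.
- **The test does not conflict with the sizing.** A chi-square test of equal proportions and a logistic test of an odds ratio of 1 address the same null hypothesis.
- **The SAP is not shown.** It may add a risk difference or further adjusted analyses, so the article's silence on the risk difference is weak evidence. The covariate point is different, because the article itself fixes the primary model.
- **The gain is modest and assumed.** At the low end it is little larger than simulation error.
- **Adjustment moves the odds ratio.** The conditional odds ratio moves further from the marginal one. This is true, and it is why the standardised risk difference belongs with the adjustment.

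These objections turn the point from an error into an efficiency improvement. They do not remove it, because the data are already collected and adjustment costs no material power even when the covariate is useless (81.4% against 81.8%, within simulation error).

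**Conclusion.** The medication-only primary analysis is valid and adequately powered on the article's own inputs. Prespecified adjustment for baseline FTND and exhaled CO would probably sharpen it: by about 1 to 4 points of power if the combined score has an odds ratio of 1.3 to 2.0 per SD, and by up to about 7 points at 2.7 per SD. Those strengths are assumptions. The documentary facts are certain, but the size of the gain is not.

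Reporting the standardised risk difference with its interval would put the result on the 12-point scale used for sizing. It would also offset the shift of the odds ratio from 1.62 to about 1.65-1.80 under adjustment. This is a worthwhile, inexpensive improvement, not an error or a contradiction in the plan.

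**What to change.** Before any outcome data by arm are examined, make these changes in the protocol's statement of the primary analysis and in the SAP:

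1. Specify the primary model as logistic regression on group, medication stratum as randomised, baseline FTND and baseline exhaled CO, the last two as continuous terms.
2. From that model, report the standardised (marginal) risk difference with 95% CI beside the odds ratio.
3. Keep the medication-only model as a sensitivity analysis.
4. State how a missing baseline FTND or CO value is handled, so that nobody drops out of the full analysis set because of it.

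The cost is wording and a short piece of programming, with no new data, visits or participants. It does change a stated primary analysis in an open-label trial, so the change should be dated and documented. Database lock is too late a limit if results by arm could be seen before then.

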### Outcomes

The primary outcome of this study will be the biochemically validated CAR from weeks 9-24. The success of smoking cessation has been defined as (1) self-reported continuous abstinence from weeks 9-24 and (2) exhaled CO concentration no more than 10 ppm at both weeks 12 and 24. In current smoking cessation programs, the CAR from weeks 13-24 drastically decreases, whereas our investigational device is expected to prevent this reduction by covering “treatment gaps” to promote the retention of appropriate recognition and behavioral changes. A single-arm prospective pilot study showed that a CASC app, even without a mobile CO checker, had a significantly higher CAR from weeks 9-24 than the historical cohort that had received standard smoking cessation program [16,17].

In addition, we will evaluate the following secondary outcomes: (1) 7-day point prevalence abstinence at weeks 4, 8, 12, 24, and 52; (2) the CAR from weeks 9-12 and from weeks 9-52; (3) changes in several scores related to smoking cessation, including the Mood and Physical Symptoms Scale (MPSS) [18], 12-item French version of the Tobacco Craving Questionnaire translated into Japanese (FTCQ-12) [19], Kano Test for Social Nicotine Dependence (KTSND) [20], and time to first lapse after initial visit; (4) usage rates of smartphone apps; and (5) the presence of product problems or adverse events.

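### The analysis section gives logistic regression and odds ratios as the only method for the secondary outcomes and does not except score changes, time to first lapse or app usage rates, which are not binary.

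*Protocol article*

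**What the plan says.** The Outcomes section of the protocol article lists five groups of secondary outcomes. Two consist of abstinence measures: "7-day point prevalence abstinence at weeks 4, 8, 12, 24, and 52", and the continuous abstinence rates (CARs) for weeks 9-12 and 9-52. The third covers "changes in several scores related to smoking cessation, including the Mood and Physical Symptoms Scale (MPSS"), FTCQ-12 and KTSND, and also "time to first lapse after initial visit". The fourth is "usage rates of smartphone apps". The fifth is the presence of product problems or adverse events.

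The Statistical Analysis section gives one method for these: "secondary outcomes at each defined period will be evaluated with logistic regression analysis adjusted for appropriate covariates between the groups". The next sentence begins "We will provide descriptive statistics, odds ratios, 95% CIs" and, with P values added, extends this reporting to every outcome. No linear, mixed, ordinal or survival model is named, and no responder cut-off is given for any scale. Further detail is deferred: "A statistical analysis plan detailing all statistical computations will be completed prior to the lock of the database".

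**The concern.** Binary logistic regression estimates the odds of a yes/no event. A change in a symptom or craving score is a quantity, time to first lapse is an event time that may be censored, and a usage rate is a rate. None has an odds ratio until someone decides where to cut it, and the protocol decides nowhere.

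An analysis plan that follows the article must therefore create cut-offs. One that uses suitable models departs from the published method. Because that plan need only be finished before database lock and the trial is described as open-label, a cut-off could be fixed late, which is a reason to correct the text itself. At stake is the information on craving, withdrawal symptoms and lapse, not the main efficacy claim.

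**Working it through.** **1. The plan's own figure.** The only size calculation is for the primary endpoint: "We estimated conservatively 52.8% in the CASC treatment group and 40.8% in the control group", 290 per arm, 80% power, chi-square test, two-sided 0.05.

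n = [1.96·√(2·p̄·(1−p̄)) + 0.842·√(p1(1−p1) + p2(1−p2))]² / (p1−p2)², with p1 = 0.528, p2 = 0.408, p̄ = 0.468. This gives 271 per arm, or 287 with continuity correction. The stated 290 agrees with the corrected value to within about 1%. Without the correction, 290 per arm gives 82.7% power. The sample size stands and does not depend on this point.

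**2. Outcome type against stated method.**

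| Secondary outcome | Type | Does binary logistic regression fit? |
|---|---|---|
| Point prevalence abstinence, five time points | binary | yes |
| CAR weeks 9-12 and 9-52 | binary | yes |
| Product problems or adverse events, present or not | binary | yes |
| Change in MPSS and FTCQ-12 (seven scheduled visits in Table 2) and in KTSND (five) | quantitative, repeated | only after a cut |
| Time to first lapse | event time | only at a fixed horizon |
| App usage rates | rate | only after a cut |

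**3. Cost of a cut for the scores (illustration).** Assumptions, since the documents give no SD or effect: normal scores with equal SD, data on all 290 per arm, and a standardised difference d of 0.20, 0.25 or 0.30.

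- Comparison of means: power = Φ(d·√(290/2) − 1.96). For d = 0.25: Φ(3.01 − 1.96) = Φ(1.05) = 85%.
- Cut midway between the arm means: the proportions above the cut are 1 − Φ(d/2) and Φ(d/2). For d = 0.25 these are 0.450 and 0.550, and the two-proportion power is 67%.
- Cut 1 SD above the control mean: proportions 0.159 and 1 − Φ(1 − d). For d = 0.25 the second is 0.227, and power is 55%.

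| d | Means | Midpoint cut | 1 SD cut |
|---|---|---|---|
| 0.20 | 67% | 48% | 38% |
| 0.25 | 85% | 67% | 55% |
| 0.30 | 95% | 82% | 71% |

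For 80% power at d = 0.25 the requirement per arm is 252 (means), 396 (midpoint cut) or 528 (1 SD cut). The ratio 396/252 = 1.57 means about 57% more participants. Its inverse, 0.64, matches the large-sample efficiency of a median split, 2/π = 0.637.

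**4. Time to first lapse (illustration).** Assume proportional hazards and lapse-free shares equal to the primary-endpoint rates. This is only a stand-in, because lapse is counted from the initial visit while the CAR starts at week 9. HR = ln 0.528 / ln 0.408 = 0.71. Events = 290 × (0.592 + 0.472) ≈ 309. Log-rank power = Φ(√309/2 × |ln 0.71| − 1.96) ≈ 85%, against 83% for a binary comparison at the horizon. Little power is lost. What a fixed-time logistic model does lose is when lapse occurred, and it needs a rule for participants not followed to the horizon. That matters here because withdrawal criterion (7) ends follow-up visits for participants still smoking at week 9, so incomplete follow-up is linked to the outcome.

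**The case against.** The strongest reply is that the sentence on secondary outcomes may cover only those with a stated period. In the Outcomes list these are the point prevalence measures and the CARs, all binary, and the abstract names just these as the main secondary outcomes. On that reading nothing is mis-assigned; the article is merely silent on the other outcomes, and silence in a condensed article with an analysis plan to follow is no fault.

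This reading is possible, but the text does not state it. The scores are also measured at defined visits (Table 2), and the promise of odds ratios is made for every outcome. The ambiguity is itself worth removing, and the same added sentences do so.

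Other parts of the reply stand:

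- A reader might infer that the plan expressly assigns logistic regression to each and every secondary outcome. It does not say so; it only fails to except the non-binary ones.
- A reader might infer that no logistic model could be fitted. Ordinal and discrete-time logistic models exist and yield odds ratios, although the protocol names neither.
- Nobody proposed a median split or any other cut, or the dropping of participants censored before lapse. The power losses describe what literal application could cost, not what the plan sets out to do.
- Separate comparisons at each visit are valid between-arm comparisons. A repeated-measures model is a choice about efficiency, not a correction of an error.

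**Conclusion.** The point holds in limited form. The article states a method and an effect measure that do not fit several outcomes it names, and it excepts none of them. That goes beyond detail left to the analysis plan.

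For the scores, the illustrative loss from a midpoint cut is 13 to 19 percentage points of power over the assumed range, and more with an extreme cut. It rests on normality and complete data on 290 per arm; with withdrawals under criterion (7), later scores will not exist for everyone. For lapse, the loss is in timing and censoring rather than power.

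It would be wrong to infer that the trial's main conclusions are at risk. The primary outcome is binary and its logistic model is adjusted for medication, the stratification factor; the main secondary outcomes are also binary. This is a minor-to-moderate correction, not one on which the trial depends.

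**What to change.** Add two or three sentences to the Statistical Analysis section and carry them into the analysis plan:

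- **Binary outcomes.** Limit logistic regression and odds ratios to point prevalence abstinence, the CARs, and presence of adverse events or product problems.
- **Score changes.** Use a linear model adjusted for baseline score and medication stratum, either ANCOVA at each visit or a repeated-measures model, and report mean differences with 95% CIs. Add a missing-data sensitivity analysis, because criterion (7) ties withdrawal to smoking status.
- **Time to first lapse.** Use a log-rank test and a Cox model stratified by medication, and report a hazard ratio. State beforehand how participants who never quit are counted.
- **App usage.** Describe it by arm, since the two apps offer different functions.

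The choice between ANCOVA and repeated measures, and the exact rule for those who never quit, can be left to the trial team provided both are fixed in advance. The change needs no new data and leaves the sample size as it is.

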## Results

A total of 580 participants with nicotine dependence will be recruited from October 2017 to September 2018 or until recruitment is complete. The final 52-week follow-up will be completed in October 2019. We expect that all trial results will be available by the end of 2019.

## Discussion

This is the first randomized controlled trial to evaluate the long-term efficacy of CASC, a smoking cessation support app for participants, which also includes a Web-based software for doctors and a mobile CO checker. We expect that participants in the CASC treatment group, in addition to a 12-week standard smoking cessation program, will exhibit a significantly higher CAR from weeks 9-24 than participants in the control app group.

In recent years, several medical apps for smartphones have shown better clinical outcomes compared with conventional treatment [10-12]. These smartphone apps have also been approved by the US Food and Drug Administration being used in daily clinical practice. In terms of smoking cessation, individuals who used CASC smartphone app without a mobile CO checker achieved 63% of the CAR from weeks 9­-24 compared with those who did not use the app (historical control) [15]. Clickotine, another smartphone app for smoking cessation, also reached 30% of the abstinence rate at 8 weeks [23]. However, it remains unclear whether CASC including a mobile CO checker (which provides exhaled CO concentrations for the user), evidence-based behavioral support, education, and counseling programs for smoking cessation is effective for maintaining long-term abstinence rates in patients with nicotine dependence.

We developed and used a mobile Internet of Things (IoT) device to measure an exhaled CO concentration level in this trial. A level of exhaled CO concentration is a useful biomarker for patients with nicotine dependence [5]. It helps them understand how much harmful CO is accumulated in their body and how steadily the harm is decreasing after smoking cessation. They might feel guilty for a high exhaled CO concentration level and try to start quitting, and in another case, they could be encouraged to keep quitting by seeing the decline of their CO level [24]. These experiences could continuously motivate them and improve adherence to the standard smoking cessation program [25].

There are several benefits to including smartphone apps with an IoT device to clinical settings. First, a mobile app covers treatment gaps between the outpatient clinic visits. It is beneficial to continuously contact participants and keep providing effective treatment programs, which could be one of the most important points for the program success [10,13]. Second, medical IoT devices enable us to easily gather biometric information remotely. Patients no longer need to access their outpatient clinics for testing; this might improve patients’ total adherence to the treatment program and could contribute to construct and promote “telemedicine.” Third, the total development costs of the app are much lower than that of medical drugs or medical devices. These apps are highly cost-effective and might reduce burgeoning medical costs [3].

Improving nicotine dependence treatment programs with therapeutic smartphone apps and IoT devices is important in terms of preventing chronic obstructive pulmonary disease, cardio- and cerebrovascular diseases, and malignant tumors. In addition, these mobile apps and devices can contribute to preventing secondhand smoke, which kills approximately 15,000 people every year in Japan [3]. In addition, our device can be a pioneer of the stand-alone programmed medical device with better treatment outcomes. Improving medical outcomes with mobile apps and devices is challenging; however, it can become a highly cost-effective treatment option in the near future. We believe that CASC, which is a combination of a smartphone app, a Web-based patient management software, and a mobile CO checker, will be able to improve the CAR, decrease smoking prevalence and passive smoking, and reduce future total medical costs, while preventing smoking-related diseases in the world.

